**Methods and analysis:**

This study is part of a wider observational study which aims to investigate the interdisciplinary factors contributing to child stunting using a ‘whole child’ paradigm. The observational study recruits women during pregnancy in Hyderabad, India, Lombok, Indonesia and Kaffrine, Senegal, and dyads (ie, 500 mother–infant pairs per country) are followed longitudinally up to 24 months after birth. Within the interdisciplinary niche, the study here has developed tools to investigate the potential exposure pathways to environmental pathogen contamination of foods and water. Holistic WASH and food safety data collection tools have been developed to explore exposure pathways at the household level, including: (1) survey questionnaires; (2) spot-checks; (3) biological sampling of drinking water, food and domestic surfaces and (4) direct observation. An integrated analytical approach will be used to triangulate the evidence in order to examine the relationships between child stunting, WASH and food safety behaviours.

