### Data collection

This WASH and food safety data collection protocol focuses on three areas: exposure pathways to wider environmental pathogens, foodborne hazards and waterborne hazards. Four data collection tools for the household-level have been developed, namely: (1) a module for WASH and food safety to be included to the cohort questionnaire-based interviews (see online supplemental appendix 1); (2) spot-checks (see online supplemental appendix 2); (3) biological sampling and (4) direct observation (see online supplemental appendix 3). The interviews and spot-checks take place simultaneously during home visits at 9, 12 and 18 months after birth. Data will be collected throughout the different seasons. Direct observation and biological sampling are conducted during a separate subsequent visit at each time point, in a subsample of the cohort. No additional inclusion or exclusion criteria were considered in the selection. Food and water samples are kept to a minimum for the analysis required, namely half filling a 50 mL Falcon tube with food served to the child, and the measure of the container in which the child is normally given drinking water, respectively.

10.1136/bmjpo-2022-001695.supp1Supplementary data

The food safety component of the data collection focuses on nutrient-rich foods with the potential to alleviate stunting, particularly on animal source foods (ASFs). This is due to their important nutritional profile,^29^ their documented potential to alleviate stunting^30–33^ and their high food safety risk profile. Selected ASFs will be considered at each country, according to their relevance.

Trained enumerators collect data using electronic tablets in all study households, as summarised in table 2. The direct observation tool is recorded on paper and enumerator positioning and previous rapport creation are used as ways to minimise bias. Privacy is maintained by stopping the direct observation on the respondent’s request. Data collection tools developed in English are translated into local languages and backtranslated into English to check for accuracy, and piloted in the field.

**Table 2 T2:** Summary of the integrated study methods and tools used to assess WASH and food safety at the household level

Tool	Description	Sample size

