### Data management and analysis

Data are collected at the households in CommCare and checked for accuracy before being transmitted to a central repository and can be downloaded in Excel for analysis. Samples are analysed at laboratories in each of the countries using tailored standard operating procedures.

Descriptive, comparative and regression analyses will be used to investigate the impact of WASH and food safety on child stunting. Factors relating to WASH and food safety amenities and practices will be considered simultaneously as external risks or preventive factors influencing the incidence and severity of stunting, using multivariable statistical approaches. To relate the main exposure variables (WASH and food safety factors) with the main outcome (stunting, measured as either z-scores or presence/absence), multivariable regressions models will be developed. According to our causal framework presented in figure 1, we will adjust this model for potential confounding factors. Some of these confounding factors will be fairly stable (eg, sex, maternal literacy, household facilities, socioeconomic status) and others will be time-varying (eg, age, breastfeeding, environmental hygiene levels). We will avoid intermediate factors (eg, infection rates). Subsequently, we will explore the potential role of the mediators in the causal framework using mediation analysis. Due to the existence of repeated measures conducted over three different time points for each child, we will account for this with a random effect term by individual in the regression model. The model will be a linear regression for stunting measured as a continuous variable, and a logistic (or ordered logistic) regression for stunting (moderate and severe) measured as a dichotomous variable. Due to the fact that in our three country settings the relevant association might differ, we will estimate the models separately in each country, and afterwards we will conduct individual participant data meta-analysis of the coefficients of interest across the countries. This strategy will allow for an optimal fit of the model in each country and at the same time we will be able to explore the heterogeneity of coefficients across countries and within subgroups (by age, sex and socioeconomic characteristics).

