## Discussion

Poor food safety and inadequate WASH, including getting in direct contact with animals, their produce and/or their faeces, are considered as important contributors to undernutrition. Cumulatively over the first 2 years of life, these factors can determine linear growth faltering. However, the causes of infant stunting are not exclusive to these factors, and therefore, it is critical to cohesively consider the myriad of determinants involved. The UKRI GCRF AASH is using an interdisciplinary approach to investigate this variety of factors causing stunting with the aim to identify solutions for the amelioration of growth and development in early childhood at the ‘whole-child’ level. Within such an interdisciplinary framework, this study design will generate comprehensive evidence on the contribution of WASH, and food safety at the household level.

Challenges to conducting integrated assessment in WASH and food safety in a multicountry study like this are various, including identifying key ASFs and key hazards in a systematic way, or the analysis of pathways linking hygiene, food and water safety, and sanitation data into the typologies of stunting. For this purpose, we developed holistic data collection tools relevant to each study setting, to measure risk factors for exposure to foodborne and waterborne disease. Multiple household-level interventions are available in both WASH and food safety but, to date, their effectiveness has not been assessed together, despite the similarity in the exposure mechanisms they are targeting. The effectiveness of relevant interventions and technologies in addressing malnutrition depends on both their biological efficacy, and the degree to which consumers adapt to and use the new approach to their contexts.^8^ We propose an approach and suggest data collection tools through which these various underlying and proximate determinants of child growth may be analysed.

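### For hygiene and contamination exposures that change between visits, a model of attained stunting over three visits with a child random effect and no stated lag mixes two associations that can differ in sign; its presence/absence outcome is prevalence, not incidence

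*Protocol article*

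**What the plan says.** All references are to the Protocol article.

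- **Exposure visits** (Data collection): "The interviews and spot-checks take place simultaneously during home visits at 9, 12 and 18 months after birth". Direct observation and biological sampling follow at a separate visit at each time point, in about one-third of the cohort.
- **Outcome** (Data management and analysis): "stunting, measured as either z-scores or presence/absence".
- **Model** (same section): "repeated measures conducted over three different time points for each child, we will account for this with a random effect term by individual". Continuous stunting gets a linear model, categorical stunting a logistic or ordered logistic one. Models are fitted by country and the coefficients are then meta-analysed. Mediation analysis follows.
- **Target** (same section): WASH and food-safety factors are considered as "influencing the incidence and severity of stunting".
- **Causal premise** (Discussion): "Cumulatively over the first 2 years of life, these factors can determine linear growth faltering".
- **Follow-up** (Abstract): dyads "are followed longitudinally up to 24 months after birth".

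No lag, cumulative exposure, change in z-score or restriction to children not yet stunted is stated. In its list of confounders, the analysis section calls household facilities fairly stable and environmental hygiene levels time-varying. The participant schedule, and so the timing of length measurement, is left to the parent cohort paper.

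**The concern.** A z-score at a visit is the sum of growth up to that visit. If exposure acts cumulatively, as the Discussion says, the exposure recorded at a visit should relate to growth over some interval, and the interval has to be named. Set against attained z-score at the same visit, a time-varying exposure yields two associations: between children (more exposed children are shorter on average) and within child (how z-score moves as exposure moves). A random-effect model with one coefficient returns a weighted average of the two. Because length is strongly correlated within a child, most of the weight can fall on the within-child part, whose sign depends on the unstated timing.

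At stake is the reading of the main coefficients for food and water contamination and observed practices. A harmful exposure could appear null or protective, and the cross-country meta-analysis would carry that forward. Families who change hygiene after poor growth would also not be separated from hygiene that affects growth.

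The second problem needs no model assumption: the target named is incidence, but the categorical outcome is status at each visit.

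**Working it through.** The article gives no effect size or power figure for this model, so there is nothing to reproduce. The check is algebra plus simulation.

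**Inputs from the article.** Visits at 9, 12 and 18 months (intervals of 3 and 6 months); 500 households per country; about one-third, or 167, for observation and sampling.

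**Assumptions, not from the article.** Same-visit pairing; random intercept only; exposure with SD 1 and the same correlation rho between any two visits; true effect b = -0.03 z per month per SD; 3 months of exposure before the 9-month visit; child SD 0.9 and residual SD 0.3 (outcome ICC 0.81/0.90 = 0.9), or 0.7 and 0.7 (ICC 0.5).

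**Within-child coefficient.** Let e1, e2, e3 be the visit-specific parts of exposure, each with variance w = 1 - rho. The stable part cancels. The within-child exposure sum of squares per child is 2w. The numerator is the sum of cov(Xj, Yj) minus one-third of cov(sum of X, sum of Y).

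*Exposure acts on the following interval.* The visit-specific parts of Y are 0, 3b·e1, and 3b·e1 + 6b·e2.
- Sum of same-visit covariances: 0.
- cov of sums: (6b + 6b)w = 12bw; one-third is 4bw.
- Coefficient: (0 - 4bw)/2w = **-2b** = +0.06, the wrong sign for any rho below 1.

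*Visit value stands for the preceding interval.* The parts of Y are 3b·e1, 3b·e1 + 3b·e2, and 3b·e1 + 3b·e2 + 6b·e3.
- Sum of same-visit covariances: (3 + 3 + 6)bw = 12bw.
- cov of sums: (9 + 6 + 6)bw = 21bw; one-third is 7bw.
- Coefficient: (12 - 7)bw/2w = **2.5b** = -0.075, the right sign.

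**How the two parts combine** (following interval, rho = 0.5). The between-child coefficient is (7b·0.5 + (12b/9)·0.5)/(0.5 + 0.5/3) = 6.25b = -0.19. The between part is down-weighted by k = 1/(1 + 3 × variance ratio).
- ICC 0.9: k = 1/(1 + 27) = 1/28. Within weight = 1/(1 + 2/28) = 0.93. Blend = 0.93(0.06) + 0.07(-0.19) = about +0.04.
- ICC 0.5: k = 1/4. Within weight = 1/(1 + 0.5) = 0.67. Blend = 0.67(0.06) + 0.33(-0.19) = about -0.02.

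**Simulation** (n = 500, 400 replicates, ICC 0.9, following interval):

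| rho | mean coefficient | wrong sign | significantly wrong |
|---|---|---|---|
| 0 | +0.057 | 100% | 100% |
| 0.3 | +0.051 | 100% | 99% |
| 0.5 | +0.041 | 99% | 83% |
| 0.7 | +0.023 | 91% | 28% |
| 0.9 | -0.038 | 7% | 0% |
| 0.97 | -0.123 | 0% | 0% |

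At ICC 0.5 the means were +0.041, +0.010, -0.024, -0.069 and -0.148 for rho 0, 0.3, 0.5, 0.7 and 0.9. Under preceding-interval timing at ICC 0.9 they ran from -0.077 to -0.166 and were never wrong-signed.

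**Subsample.** The most variable measures come from about 167 children. Expected coefficients do not change, but the spread grows by √(500/167) = 1.73. At rho = 0.5, SD 0.014 becomes 0.024, so a mean of 0.041 is about 1.7 SDs from zero: still usually wrong-signed, but far less often significant.

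**Interval model.** Regressing monthly change in z-score on the exposure that applies to that interval gave -0.0297 to -0.0303 throughout, against a true -0.03. If the start-of-interval exposure is used when the visit value really stands for the preceding interval, the slope is rho·b (rho = 0.5 gives -0.015): attenuated, not reversed.

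**Incidence.** A child stunted at 9, 12 and 18 months supplies three positive records and no new case after 9 months. A child first stunted at 18 months supplies one positive record and one new case. Odds fitted to all records therefore describe prevalence.

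**The case against.** The strongest reply is that the premise is inferred. The article says neither that exposure and outcome come from the same visit nor that the random effect is an intercept only. Pairing exposure at 9, 12 and 18 months with length at 12, 18 and 24 months would also give three records per child, and a fuller plan may specify that. This stands, and it limits the point to what the stated model gives on its natural reading.

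It also stands that reversal is conditional. Many items are standing conditions, such as toilet type, handwashing station, refrigerator and water source. For these a 9-month record can represent earlier months and persistence is high, so reversal is not expected.

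Several stronger readings are tempting but unsupported:

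- *That exposure recorded at 9 months cannot have affected length at 9 months.* It can, if it stands for the months before.
- *That the model recovers only a small fraction of the truth.* Setting -0.077 against the sustained 12-month effect of 12 × (-0.03) = -0.36 gives about 21%, but a per-visit slope and an accumulated effect are different quantities. Against one 3-month interval (-0.09) the same slope is about 86%.
- *That birth and 24-month length are excluded, prenatal deficit is ignored, or mediation lacks time order.* The length schedule is in the parent paper, confounders are listed only as examples, and the visits used for mediation are not stated.

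On incidence, one can say the word is used loosely and no rate is promised. That makes the correction easy, but the mismatch remains.

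**Conclusion.** The point holds in a conditional form. For exposures that change between visits, the model as described yields a coefficient that blends within-child and between-child associations and need not carry the sign of the true effect. The within-child part is -2b or 2.5b depending only on which interval the visit value represents. Across the scenarios run at outcome ICC 0.9, one true effect of -0.03 per month gave fitted coefficients from +0.057 to -0.166.

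This rests on same-visit pairing, a random intercept, and assumed persistence and ICC. The article gives no figure that puts the study inside or outside the region where the sign reverses. A reader might infer that the study will report harm as null or protective; the document does not support that as a prediction, and for stable facilities or preceding-interval timing it is not expected.

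The incidence point holds on the text alone: presence/absence at each visit is prevalence.

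**What to change.** 1. State, for each time-varying exposure, which period the visit value represents and which length measurement it is related to.
2. For these exposures add an interval model: change in z-score per month from one visit to the next, on exposure at the start of the interval. Extend it to 24 months if the parent cohort measures length then.
3. Where the random-effect model is kept, split exposure into the child's mean and the deviation from it, and report the two coefficients separately.
4. For stable facilities keep a between-child or cumulative-mean exposure model, without adjusting for 9-month length, which would remove growth already lost by then.
5. Order the mediation as exposure, then infection, then later z-score.
6. Model incidence as first stunting among children not stunted at the previous visit, or call the outcome prevalence.

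Cost: plan wording and some extra analysis, with no new data collection. In the interval model the 9-month length becomes a baseline rather than an outcome record, and effects accumulated before 9 months are not captured there. That is why item 4 is kept alongside it. If the visit value really reflects the preceding interval, the start-of-interval slope is attenuated, so item 1 matters.

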**Figure 1 F1:**
[figure not shown]
A conceptual framework showing the linkages of WASH and food safety with stunting at the household level. WASH, water, sanitation and hygiene.

In theory, access to adequate WASH facilities enables appropriate drinking water, hygiene and food safety practices, contributing to reduction in transmission of foodborne and waterborne pathogens and improving nutrient uptake, and ultimately child growth and development.^20^ Drinking water may be contaminated at the point of supply, or through transport and storage.^15 16^ The availability of clean water is critical for optimal hygiene practices,^10^ to address contamination by human and animal faeces,^22^ and to prepare food hygienically. Sanitation facilities can enable safe faeces disposal, especially those of young children, which can be particularly pathogenic.^23^ Faecal contamination can also come from the presence of domestic and wild animals or pests inside the household or in surrounding spaces.^24^ It is expected that these sources of infection become more important as a child starts crawling and interacting with their environment. As such, understanding of the determinants of food and hygiene practises in the household is key to improving infant health and nutrition.^25^

Along with direct exposure, there is also an indirect route from water supply and sanitation facilities to childhood malnutrition, which operates through the opportunity costs of resource use. The time carers have to observe, correct, and address unhygienic behaviour, and the scarcity of time in relation to competing activities that need to be done by carers in the home or workplace, may also be detrimental for children’s nutritional outcomes.^26^ For example, it is typically women and older children, both of whom are more likely than others to be carers of young children, who spend time fetching water, engaging with animal fodder and collecting firewood. This may occur at the expense of adequate childcare and feeding, food preparation, education or rest.^27^ When drinking water needs cannot be met affordably, households may need to purchase less food in order to afford enough water to drink. This kind of trade-off is clearly more prevalent for the poorest households, for whom malnutrition is also likely to be highest.

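### A single random effect per child forces equal correlation across visits 3, 6 and 9 months apart; if correlation decays, z-score intervals for exposure-by-age slopes and late-changing exposures are too narrow

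*Protocol article*

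**What the plan says.** In the protocol article, the section on data management and analysis gives one device for dependence within a child: "Due to the existence of repeated measures conducted over three different time points for each child", the authors state, "we will account for this with a random effect term by individual in the regression model". For z-scores, "The model will be a linear regression for stunting measured as a continuous variable". Models are fitted separately by country and then combined. The section names no random slope, serial correlation, unstructured covariance or robust standard error.

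The data collection section sets the visits: "The interviews and spot-checks take place simultaneously during home visits at 9, 12 and 18 months after birth". The gaps are therefore 3 months (9 to 12), 6 months (12 to 18) and 9 months (9 to 18).

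Three other statements bear on the choice:

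- The discussion says of WASH and food safety factors: "Cumulatively over the first 2 years of life, these factors can determine linear growth faltering".
- The conceptual framework says: "It is expected that these sources of infection become more important as a child starts crawling and interacting with their environment".
- The analysis section intends to "explore the heterogeneity of coefficients across countries and within subgroups (by age, sex and socioeconomic characteristics"). It also lists covariates that vary over time.

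**The concern.** A random intercept with independent residuals makes any two visits of the same child equally correlated. Growth measurements usually resemble each other less as they move apart, and faltering that builds up over two years would act in that direction. If so, the model overstates the 9-18 month correlation and understates the 9-12 month one.

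The quantities affected are those that compare a child with itself over time: whether an exposure matters more at later ages, and the effect of an exposure that changes between visits. The article shows interest in both. Understated standard errors for age slopes would produce too many apparent age-dependent effects. For exposures that come and go, the cost is mainly wasted information.

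**Working it through.** **Inputs.** From the article: three visits at 9, 12 and 18 months, one random effect per child, a linear model for z-scores, 500 households per country. The article gives no correlation, SD, effect size or alpha, so there is no figure of its own to reproduce. Assumed: equal variances (set to 1), visit means fitted, and two sets of true correlations r(9-12)/r(12-18)/r(9-18): a stronger decay, 0.90/0.80/0.70, and a milder one, 0.80/0.75/0.70.

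**What the model imposes.** In large samples the random-intercept fit settles on the mean correlation m: 0.80 for the stronger decay, 0.75 for the milder. For each contrast, let R be model-based SE divided by true SE. Coverage of a nominal 95% interval is 2Φ(1.96R) − 1. R does not depend on the number of children.

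**Exposure-by-age slope.** Ages minus their mean of 13 are −4, −1 and 5, with sum of squares 42. The variance of the slope numerator is:

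- True: 42 + 8·r(9-12) − 40·r(9-18) − 10·r(12-18)
- Model: 42(1 − m)

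Stronger decay: true 42 + 7.2 − 28 − 8 = 13.2; model 42 × 0.20 = 8.4; R = √(8.4/13.2) = 0.80; coverage 88.2%.

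Milder decay: true 42 + 6.4 − 28 − 7.5 = 12.9; model 42 × 0.25 = 10.5; R = √(10.5/12.9) = 0.90; coverage 92.3%.

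**Visit contrasts for a stable exposure.** R = √((1 − m)/(1 − r)), with r the true correlation of the two visits.

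- 18 v 9 months: √(0.20/0.30) = 0.82, coverage 89.0% (stronger); √(0.25/0.30) = 0.91, coverage 92.6% (milder).
- 12 v 9 months: √(0.20/0.10) = 1.41, coverage 99.4% (stronger); √(0.25/0.20) = 1.12, coverage 97.2% (milder). This interval is too wide.

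**Exposure that differs between children at one visit only.** Put k = m/(1 + 2m), weight 1 − k on that visit and −k on the other two, and let q be the true variance of that weighted sum. Then R² = (1 − m)(1 − k)/q.

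- Change seen only at 18 months: stronger, k = 0.308, q = 0.200, R² = 0.20 × 0.692/0.200 = 0.69, R = 0.83, coverage 89.7%. Milder, k = 0.30, q = 0.205, R² = 0.25 × 0.70/0.205 = 0.85, R = 0.92, coverage 93.0%.
- Present only at 12 months: stronger, q = 0.077, R² = 0.20 × 0.692/0.077 = 1.80, R = 1.34, coverage 99.1%. Too wide.

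**Exposure varying independently at each visit.** With equal variances only the mean correlation enters the standard error, so R = 1.00 and coverage is 95%. The cost is efficiency. The ratio of variance to that of the correctly weighted estimate is the trace of the inverse true correlation matrix over that of the inverse equal-correlation matrix.

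- Stronger: (0.36 + 0.51 + 0.19)/0.068 = 15.59, against 3 × 0.692/0.20 = 10.38; ratio 1.50.
- Milder: (0.4375 + 0.51 + 0.36)/0.1475 = 8.86, against 3 × 0.70/0.25 = 8.40; ratio 1.06.

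An exposure that switches on and off with some persistence has coverage of 92-95% under the stronger decay.

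**Average effect of a stable exposure.** The variance of a child's total is 3 + 6m under both the model and the truth, so R = 1.00 and coverage is 95%.

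**Cross-checks.** A simulation with 500 children, three visits and 2,000 runs gave 11.9% false positives for exposure-by-age at 0.90/0.80/0.70 (formula: 11.8%), and 7.2-11.9% over five other decaying structures. Unstructured covariance brought these back to 4-6%. Over further assumed structures (serial correlation, measurement error, rising SD) age-slope coverage was 88.4-90.2%, and the precision loss for age interactions was 0-3%. The efficiency gain for a fluctuating exposure fell to about 1% in one structure with 20% measurement error. With truly equal correlations all intervals are right and the unstructured model loses nothing (variance ratio 1.00-1.01).

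**The case against.** The strongest reply is that a journal article condenses its analysis. It does not say that the intercept is the only dependence term or that standard errors are model-based; a fuller plan may add a random slope or robust errors. This stands in part. Robust standard errors would repair the intervals in the linear model, though not the lost efficiency. But the article does not leave the matter open: it names a device, and the point concerns that choice.

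Second, the statement on cumulative faltering concerns causes of growth, not residual correlation of age-standardised z-scores after adjustment. That is right. Decay is plausible, not shown, and a reader who infers that the article's own design contradicts its model goes too far. Unequal spacing alone contradicts nothing.

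Third, a reader might infer that intervals for changing exposures are generally wrong in both directions. The working does not support this: too-wide intervals arise only for special patterns, such as exposure at 12 months only or the 12 v 9 month contrast. Nor is precision lost across the board, since age interactions lose almost none.

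Fourth, age heterogeneity is exploratory, and the article fixes no exposure-by-age term. If age subgroups were analysed one visit at a time, within-child covariance would not enter. This limits the weight of the point; the stated repeated-measures model still carries the restriction.

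Finally, the logistic and ordered logistic models were not computed, so nothing is concluded about them.

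**Conclusion.** The point holds for the linear z-score model, read plainly, and is conditional on correlation falling with the gap between visits. Under that assumption, intervals for exposure-by-age slopes are too narrow (about 88-92% coverage over the two assumed sets), and so are those for exposures that change late (about 90-93%). Ordinary fluctuating exposures have intervals that are about right to slightly narrow, with estimates less efficient than they need be; how much less depends heavily on the assumed decay and measurement error.

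A reader might go on to doubt the main associations. The documents and the arithmetic do not support that: the average effect of a stable exposure keeps its nominal coverage. The point is worth a change of wording because the affected contrasts are ones the authors intend to explore and the remedy is cheap.

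**What to change.** For the linear z-score model only, replace the sentence on the individual random effect with: *Repeated measures are handled with an unstructured 3x3 within-child covariance over the 9, 12 and 18 month visits, with child-level robust standard errors.*

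The cost is one sentence and four more covariance parameters (three variances and three covariances, six in all, against two for a random intercept), with about 500 children per country. No new data are needed. No change is proposed for the logistic model.
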